#### Feasibility of Reality DTx^®^

Study parameters to evaluate clinical feasibility (safety, adherence, user experience) of the Reality DTx^®^ intervention will be compared between the two groups (HoloLens 2, Magic Leap 2) using independent-sample *t*-tests. The Shapiro–Wilk test will be used to check for normality. If the data is not normally distributed, the Mann–Whitney *U*-test will be used. Weekly scores of feasibility parameters (e.g. adherence scores over the intervention period) will undergo 2 (between-subjects factor Group: HoloLens 2 vs Magic Leap 2) × 6 (within-subjects factor Weeks: week 1 to 6) mixed ANOVA.

#### Potential efficacy of Reality DTx^®^

The study parameters to evaluate potential efficacy of the Reality DTx^®^ intervention will be subjected to a 2 × 3 mixed ANOVA with the within-subject factor Time (three levels: t0, t1, and t2) and the between-subjects factor Group (two levels: HoloLens 2, Magic Leap 2). The assumption of sphericity will be checked according to Girden [56]. If Greenhouse–Geisser’s epsilon exceeds 0.75, the Huynh–Feldt correction will be applied; otherwise, the Greenhouse–Geisser correction will be used. Effect sizes will be quantified with $${{\eta }_{p}}^{2}$$.

Paired-sample *t*-tests will be used for post hoc comparisons of significant main and/or interaction effects involving the factor Time (or paired-sample Wilcoxon tests if data is not normally distributed according to the Shapiro–Wilk test). We expect no main effect of Group, nor a Time by Group interaction, but only a main effect of Time, with superior performance after the Reality DTx^®^ intervention (t2) than before (t0, t1). In case t1 differs significantly from t0 as well (which may suggest learning/habituation in repeated test performance), an additional test on difference scores will then be performed to compare the magnitudes of intervention (t2–t1) and learning/habituation (t1–t0) effects with a paired-samples *t*-test (or paired-samples Wilcoxon tests if data is not normally distributed according to the Shapiro–Wilk test). We expect that potential intervention effects will be greater in magnitude than potential learning/habitation effects.

Because this is a feasibility trial, these comparisons will also be evaluated with Bayesian hypothesis testing [57, 58] using JASP [55], quantifying how much more likely the data support the alternative hypothesis (gait-and-balance outcomes differ over Time or Groups) compared to the null-hypothesis (gait-and-balance outcomes do not differ over Time or Groups), reported as the Bayes factor BF_10_ (alternative/null). In line with Jeffreys [57], we regard BF_10_-values between 1 and 3 as anecdotal evidence, values between 3 and 10 as moderate evidence, and values above 10 as strong evidence for the alternative hypotheses.

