## Methods

### Trial design

This clinical feasibility trial protocol is designed as a waitlist-controlled 6-week home-based AR gait-and-balance exergaming intervention, in which the type of AR glasses (Magic Leap 2, HoloLens 2) will be counterbalanced over participants (Table 1). All participants will start with a 6-week waitlist period, followed by the 6-week home-based AR therapeutic gait-and-balance exergaming intervention Reality DTx^®^. Baseline (t0), pre-intervention (t1), and post-intervention (t2) repeated measurements will be conducted to compare within-participant Reality DTx^®^ intervention effects against usual care (i.e. does t2–t1 differ from t1–t0?) while controlling for potential learning effects in outcomes over repeated measurements (i.e. does t1–t0 systematically deviate from 0?). Between-group comparisons will be performed to evaluate potential AR glasses superiority (i.e. does t2–t1 differ between HoloLens 2 and Magic Leap 2 subgroups)? Feasibility of the Reality DTx^®^ intervention will be examined in terms of safety, adherence, and user experience (i.e. usability and acceptability), including an evaluation of AR glasses superiority in that regard.

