### Sample size

For the proposed study, in which Reality DTx^®^ therapeutic gait-and-balance exergaming will for the first time be used independently at home, we will include a convenience sample of 24 participants to evaluate its initial feasibility (safety, adherence, and user experience) and potential efficacy for improving gait and balance. This sample size fits this type of study and is logistically feasible given the associated number of laboratory visits (72), weekly telephone calls (120), and home visits (24) vis-à-vis the availability of the gait laboratory and personnel, project duration, and funding. In addition, a sample of 24 participants is sufficient to evaluate the potential efficacy of this exergaming intervention. That is, with 95% power, a one-tailed alpha error of 5% and an expected minimum improvement of 1.63 s on the Timed Up-and-Go test (i.e. smallest detectable difference [42], a sample size of 18 is required to detect an effect with an effect size of 0.815 (Cohen’s *d* statistic; SD over repeated measurements 2.0 s [43]). This a priori required sample size calculation for differences between two dependent means was calculated with G*Power 3.1.9.7.

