### Future steps after this feasibility trial

The results on feasibility and potential efficacy will identify methodological challenges for future randomised controlled trials [73] and form the basis for design choices (e.g. required sample size, primary outcome measures) regarding the effectiveness of home-based AR gait-and-balance interventions for pwPD. Specifically, the complementary selection of outcome measures, quantifying various aspects of gait and balance such as walking adaptability, dynamic balance, and strength, will give a comprehensive insight into the specific constructs tackled with Reality DTx^®^ exergaming while the scores from baseline, pre-intervention, and post-intervention assessments will provide indications of obtainable effect sizes. Together, this will inform about the most specific and sensitive outcome measures to demonstrate gait-and-balance effects with remotely monitored and prescribed home-based AR therapeutic exergaming.

Such future studies will contribute to solving a societally important problem: accessibility to treatment. PD is a growing disease, and the number of pwPD is expected to double in the next two decades. This will increase the burden on already understaffed care, resulting in longer waitlists and suboptimal treatment. Technology like Reality DTx^®^ to safely deliver effective treatment (partly) at home may help counter this doom scenario, allowing pwPD to complete personalised and monitored therapeutic gait-and-balance exercises of the right frequency, intensity, with high levels of repetition, type, and duration in the convenience of their own home (saving time, costs, and burden associated with travelling to the healthcare professional) and own time (exercising whenever they feel ready, taking into account fatigue, medication effects and matters of work, household, and family), while potentially saving the healthcare system time and costs (the same healthcare professional can treat more pwPD). Being able to remotely monitor adherence and performance of the gait-and-balance exercises is crucial to guard the quality of treatment and to personalise treatment frequency, intensity, type, and time. With the pwPD participating in this feasibility trial, we will evaluate safety, adherence, acceptability, and usability of such a new care model supported by AR technology while future randomised controlled trials should address its effect and cost-effectiveness.

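### The only efficacy effect size named, partial eta squared, cannot tell a waitlist gain from an intervention gain for the Time effect, and none is named for t2–t1 or for the contrast that the design poses

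*Protocol article*

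**What the plan says.** Trial design states the within-participant efficacy question without any condition: "does t2–t1 differ from t1–t0". The waitlist period is there to supply the comparison and to expose learning over repeated testing.

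Statistical analysis, Potential efficacy, sets a 2×3 mixed ANOVA (Group by Time) for each efficacy outcome. In that paragraph, "Effect sizes will be quantified with" partial eta squared. Paired tests follow if an effect involving Time is significant. A test comparing the two change scores follows only if t1 also differs significantly from t0. The section then says that these comparisons will also be assessed with Bayes factors, and words the null as "gait-and-balance outcomes do not differ over Time or Groups".

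Future steps says that the results will inform design choices for later randomised trials, including sample size and primary outcome, and that "the scores from baseline, pre-intervention, and post-intervention assessments will provide indications of obtainable effect sizes".

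**The concern.** The omnibus Time effect measures how far the three visit means spread around their average. It takes no account of which visit moved or in which direction. A participant group that improves on retesting during the waitlist and then stays flat can produce the same partial eta squared, and the same Bayes factor against no difference over Time, as a group that is flat during the waitlist and improves under the intervention.

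The summaries that the section spells out therefore do not measure the quantity that the design asks about. The trial is also meant to help identify the most sensitive outcomes and to indicate obtainable effects. If outcomes were compared on partial eta squared of Time, those with large practice gains would rank high for the wrong reason.

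**Working it through.** **Inputs.** From Sample size: "a one-tailed alpha error of 5% and an expected minimum improvement of 1.63 s on the Timed Up-and-Go test"; "a sample size of 18 is required to detect an effect with an effect size of 0.815"; "SD over repeated measurements 2.0 s"; and a "convenience sample of 24 participants". Assumptions of this check: 12 participants per glasses group, an SD of 2.0 s for each of the two changes, and a correlation between the two changes from –0.5 (sphericity) to 0.

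**The plan's own figure.** d = 1.63/2.0 = 0.815. The exact one-sided paired t-test at 5% has power 0.942 at n = 17 and 0.953 at n = 18. The stated 18 reproduces.

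**Partial eta squared of Time, sphericity.** The expression is n·SS / (n·SS + df₂·σ²), where SS is the sum of squared deviations of the visit means, df₂ = 2 × 22 = 44 and σ² = 2.0²/2 = 2.

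- Intervention only, means (0, 0, –1.63): SS = (2/3) × 1.63² = 1.771.
- One-off practice, means (0, –1.63, –1.63): SS is again 1.771.
- Steady practice, means (0, –0.94, –1.88): SS is again 1.771, by choice of the step.

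All three give 24 × 1.771 / (24 × 1.771 + 44 × 2) = 42.5/130.5 = 0.326. The noncentrality is 42.5/2 = 21.3 and the power of the Time test is 0.984. The mean t2–t1 is –1.63, 0.00 and –0.94 s respectively.

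**Simulation, 20,000 trials per pattern, correlation –0.5 to 0.**

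| Pattern | Mean partial eta squared | Time test significant | t2–t1 significant improvement |
|---|---|---|---|
| Intervention only, 1.63 s | 0.28–0.34 | 92–98% | about 97% |
| One-off practice, 1.63 s | 0.28–0.34 | 92–98% | about 2.5% |
| Steady practice, 0.815 s per visit | 0.23–0.29 | about 80–94% | about 48% |

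**Bayes factor.** A BIC approximation, exp{–½[48·ln(1 – partial eta squared) + 2·ln 48]}, gives about 446 at a partial eta squared of 0.34. This far exceeds the protocol's threshold of 10 for strong evidence, and it applies equally to the three patterns with equal SS. It is not JASP's default-prior value, so only the equality across patterns should be relied on.

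**The condition on the net contrast.** Under steady practice of 0.815 s per visit, the true net contrast is zero. In 24–32% of simulated trials the Time effect and the t2–t1 improvement are both significant while t1–t0 is not, so the change-score comparison is never run.

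**The net contrast (t2–t1)–(t1–t0).** Its mean is –1.63 s for intervention only, +1.63 s for one-off practice and 0 for steady practice, so it separates the patterns. Its SD is 2.0 × √[2(1 – r)]: 3.46 s at r = –0.5 and 2.83 s at r = 0. The standardised effect for intervention only is 1.63/3.46 = 0.47 to 1.63/2.83 = 0.58. Two-sided 5% power at n = 24 is 0.60 to 0.77.

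**The case against.** A reader might infer that the plan cannot distinguish practice from intervention at all, or that partial eta squared and BF10 are the figures that will size the next trial. The document supports neither.

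- The planned paired tests resolve the one-off practice case almost completely, and the section states that t2 is expected to be better than both t0 and t1. Nothing there treats a significant Time effect as proof of benefit.
- Future steps ties obtainable effects to the scores at the three assessments. Both t2–t1 and the net contrast can be computed from those scores. Use of partial eta squared for sizing is an inference.
- The Bayesian sentence comes after the ANOVA, the paired tests and the change-score test, so it can be read to cover all of them. The wording about Time or Groups may be only a general gloss.
- Steady practice is a constructed pattern. No figure in the document supports its size.
- Partial eta squared is a conventional ANOVA summary, and a condensed article leaves reporting detail to the full protocol.

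These arguments limit the point but do not remove it. The paired tests yield decisions, and no effect size is named for them. On the wider reading, the net contrast's Bayes factor still inherits the condition on t1–t0, and no stated hypothesis is equal change in both periods. The article does not merely omit detail: it fixes an effect size and hypotheses that do not match its own design question.

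**Conclusion.** The point holds as a mismatch between the stated efficacy summaries and the stated efficacy question. For the Time effect, partial eta squared and a Bayes factor against no difference over Time do not depend on visit order. A 1.63 s gain in either period gives a mean partial eta squared of 0.28–0.34, assuming 24 participants, an SD of 2.0 s for each change and a correlation between changes of –0.5 to 0. That both summaries ignore visit order does not depend on these inputs; the particular values do. No figure stated in the protocol is wrong on this point, and the planned t2 versus t1 test protects against mistaking a one-off practice gain for benefit. What is missing from the fixed analysis is a signed, unconditional estimate of the quantity that the waitlist design was built to measure. The change is worth making, but it does not threaten the trial.

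**What to change.** In Potential efficacy, state that for each efficacy outcome the mean, 95% CI and SD of t2–t1, of t1–t0 and of (t2–t1)–(t1–t0) will be reported in original units, whatever the Time test or the t1–t0 test shows. For the last of these, add a directional Bayes factor: greater improvement in the intervention period against equal change in both. The direction matters, because a two-sided Bayes factor would be the same size for a net contrast of +1.63 s as for –1.63 s. Partial eta squared may stay as a descriptive ANOVA statistic. In Future steps, name the signed estimates, not partial eta squared, as the basis for effect sizes and outcome choice.

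The cost is a few lines of wording and output from data already planned. The drawback is that the net contrast is less precise than t2–t1 (standardised effect 0.47–0.58 against 0.815; two-sided power about 0.60–0.77 for a 1.63 s intervention-only effect). It also understates the intervention effect when practice is one-off, so it should be read together with t2–t1 and t1–t0.

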**Fig. 1 Fig1:**
[figure not shown]
Augmented-reality (AR) glasses (Magic Leap 2 (**A**) and HoloLens 2 (**B**)) for performing gait-and-balance exercises at home using Reality DTx^®^ therapeutic exergames. In (**C**), ‘Smash’ is illustrated, an AR boxing game promoting weight shifts, dynamic balance, turning, and walking with direct feedback on task duration, number of required punches, and number of smashed holograms like the depicted vase)

Reality DTx^®^ is specifically designed for pwPD to improve their gait and balance, both in clinic and at home, with AR exercises being gamified, personalised, and accessible (at any time) to maximise adherence. Hence, Reality DTx^®^ can be regarded as AR therapeutic exergaming intervention, a combination of gait-and-balance exercises and gaming delivered through wearable AR glasses. Taking into account the low adherence to prescribed exercises by PD physiotherapists in standard care [20], a home-based AR gait-and-balance exergaming intervention like Reality DTx^®^ might improve the ease of accessibility to therapeutic exercises and therefore increase exercise adherence, help achieving the prescribed required number of repetitions, and potentially its effect through personalised interventions (e.g. following FITT principles), motivational feedback, and remote monitoring by the therapist.

In this clinical feasibility study, we evaluate a 6-week remotely prescribed and monitored home-based AR gait-and-balance exergaming intervention for pwPD (Reality DTx^®^). The primary objective is to evaluate its feasibility (in terms of safety, adherence, and user experience [usability and acceptability]) and potential efficacy for improving gait and balance (in terms of standard clinical and laboratory-based gait-and-balance test outcomes and targeted walking-related fall-risk indicators). The secondary objective is to examine AR glasses’ superiority (i.e. potential differences between Magic Leap 2 and HoloLens 2 subgroups) in those regards. In this study protocol, we outline the methods used to reach both objectives and discuss potential implications for future research and clinical practice.

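### For the efficacy outcomes, the analysis section has no test that isolates the between-glasses difference in t2–t1 that the Trial design section asks about

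*Protocol article*

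**What the plan says.** The Background section sets the secondary objective for both feasibility and efficacy: "The secondary objective is to examine AR glasses’ superiority (i.e. potential differences between Magic Leap 2 and HoloLens 2 subgroups) in those regards". The Trial design section turns the efficacy part into a specific between-group question: "does t2–t1 differ between HoloLens 2 and Magic Leap 2 subgroups".

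Under Statistical analysis, the two halves of that objective are handled differently.

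- **Feasibility.** Parameters "will be compared between the two groups (HoloLens 2, Magic Leap 2) using independent-sample *t*-tests", or by Mann–Whitney U if not normal. Weekly scores go into a Group by Weeks mixed ANOVA.
- **Efficacy.** Outcomes go into a "2 × 3 mixed ANOVA with the within-subject factor Time (three levels: t0, t1, and t2) and the between-subjects factor Group", with partial eta-squared as effect size. Paired t-tests or Wilcoxon tests "will be used for post hoc comparisons of significant main and/or interaction effects involving the factor Time". If t1 differs from t0, a further paired test compares t2–t1 with t1–t0. The same comparisons are repeated with Bayes factors, the alternative being that "gait-and-balance outcomes differ over Time or Groups".

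The stated expectation is: "We expect no main effect of Group, nor a Time by Group interaction, but only a main effect of Time".

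**The concern.** The design section asks about one contrast: the difference between two randomised subgroups in change from t1 to t2. The efficacy analysis names its tests, follow-ups included, and none of them is that contrast.

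- The Group main effect averages t0, t1 and t2. Nobody has trained at home with either device at t0 or t1, so two thirds of the average carries no device effect.
- The interaction has 2 degrees of freedom. It covers t1–t0 as well as t2–t1, so significance does not show in which period the groups diverged.
- The follow-ups are paired. They describe change within people and cannot show that two independent subgroups differ.
- Partial eta-squared for a 2-df term gives neither the direction nor the size of a difference between glasses.

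Two misreadings are at stake. A null Group main effect, which the plan expects, could be taken as evidence about the glasses although that test is almost blind to a device effect. After a significant interaction, improvement in one subgroup but not in the other could be taken as superiority.

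**Working it through.** **1. The plan's own figure.** The Sample size section gives an improvement of 1.63 s on the Timed Up-and-Go, SD 2.0 s, one-tailed 5%, 95% power, N = 18. Here d = 1.63/2.0 = 0.815. A paired t-test with the noncentral t distribution gives power 0.953 at N = 18 and 0.987 at N = 24, so the figure reproduces. It concerns the within-person comparison only; the document gives no effect size for the glasses.

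**2. Inputs for the glasses comparison.**
- From the document: 24 participants split equally, so 12 per group; visits t0, t1 and t2; home use only after t1.
- Assumed: a difference of 1.63 s at t2 only, SD of change 2.0 s (both borrowed from the sample-size section), equal correlation r between visits, r = 0.5–0.9, two-sided 5%.
- With SD of change 2.0 s, the within-person variance per visit is 2.0²/2 = 2, and the total variance per visit is σ² = 2/(1 − r).

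**3. Group main effect.** The expected estimate is 1.63/3 = 0.54 s, with SE = √[σ²·(1 + 2r)/3·(2/12)].
- r = 0.5: σ² = 4, SE = 0.667, noncentrality 0.815, power 0.12.
- r = 0.9: σ² = 20, SE = 1.764, noncentrality 0.308, power 0.06.

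**4. Time by Group interaction.** Noncentrality λ = 12·(1.63²/3)/2 = 5.31 on F(2, 44), giving power 0.50 whatever r is.

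**5. Direct test of t2–t1.** SE = 2.0·√(2/12) = 0.816, noncentrality 2.00, 22 df, power 0.48. With 12 per group, 80% power needs a difference of about 2.4 s; for 1.63 s it needs about 25 per group.

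**6. ANCOVA of t2 on glasses with t1 and t0.** Residual variance = σ²·[1 − 2r²/(1 + r)], 20 df.
- r = 0.5: 2.67, SE = √(2.67/6) = 0.667, noncentrality 2.44, power 0.64.
- r = 0.9: 2.95, SE = 0.701, noncentrality 2.33, power 0.60.

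**7. The same comparison in SD units** (device effect at t2 only, σ = 1, 12 per group):

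| r, effect | Group main effect | Interaction | ANCOVA on t1 | ANCOVA on t1 and t0 |
|---|---|---|---|---|
| 0.8, 0.8 SD | 10% | 88% | 88% | 93% |
| 0.8, 1.0 SD | 13% | 98% | 97% | 99% |
| 0.6, 1.0 SD | 15% | 79% | 83% | 88% |

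The main effect is weak throughout. The interaction is close to one-covariate ANCOVA, and the second covariate adds a little more.

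**8. Specificity** (simulation, 20,000 trials, r = 0.8). With a 1.63 s difference at t2 only, the interaction rejects in 50% of trials and the direct t2–t1 test in 48%. With the same difference at t0 only, they reject in 50% and 4.8%. With no difference, both reject in 5.0%. The interaction cannot tell the first two situations apart; the direct contrast can.

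**The case against.** A reader might infer that the glasses are never compared and that the secondary objective goes unanswered. The document does not support that. The interaction is a planned between-group test of differential change, named in the statement "We expect no main effect of Group, nor a Time by Group interaction", and its power is close to that of the direct alternatives. The feasibility half of the objective has its own independent-samples tests. Setting the Group main effect alone against ANCOVA would therefore exaggerate the loss.

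A reader might also infer a high risk of false superiority claims from separate subgroup tests. If both subgroups truly improve with a standardised paired effect of 0.6, each paired test with n = 12 has power 0.475, and exactly one is significant with probability 2·0.475·0.525 = 0.50. But the plan runs paired tests only after a significant effect. When both subgroups change equally at every step, the interaction is significant in about 5% of trials, which caps this route near 5%.

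Third, glasses are block-randomised and no training takes place between t0 and t1. A group difference over that period is then essentially chance and lies within the nominal error rate. The t0-only scenario shows what the interaction responds to, not what is likely to happen.

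Fourth, the design section does state the contrast, and a condensed article may leave its formula to an analysis plan. Nor does the document say that a null result will be read as equal glasses.

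These points limit the finding but do not remove it. The analysis section names its follow-ups explicitly, they are all within-person, and a significant interaction would still leave the stated question without a signed between-glasses estimate.

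**Conclusion.** The point holds for the efficacy outcomes only: the contrast in the Trial design section has no matching test under Statistical analysis. The Group main effect is uninformative about the glasses, with power of about 6–15% across the assumed scenarios. The interaction is a valid omnibus test of differential change with good relative power, but it does not isolate t2–t1, and its named follow-ups do not compare the glasses.

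The remedy mainly brings specificity and an interpretable estimate. The gain in power is modest and comes from covariate adjustment; an unadjusted test of t2–t1 has 0.48 against 0.50 for the interaction, so it improves specificity alone. All power figures rest on assumed glasses differences, equal visit correlations and 12 per group. The trial remains small for this question under any of these analyses.

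**What to change.** In the efficacy part of Statistical analysis, make the glasses comparison for each outcome an ANCOVA of t2 on glasses, with t1 and t0 as covariates. Report the adjusted difference with its 95% CI and a Bayes factor for that difference. At minimum, specify a 1-df independent-samples contrast of t2–t1, which matches the design section's wording directly.

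State that neither the Group main effect nor separate within-subgroup paired tests will be used as evidence about the glasses. The mixed ANOVA can stay for the Time question, and the feasibility comparisons need no change.

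The cost is wording and two covariate degrees of freedom (20 error df instead of 22). All three measurements are already scheduled for every efficacy outcome.

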## Background

For people with Parkinson’s disease (pwPD), gait-and-balance impairments are common and disabling. Gait impairments are varied across pwPD but are typically continuous in nature (shuffling, slow, and asymmetrical gait pattern) and can also become episodic when the disease progresses (i.e. freezing of gait) [1, 2]. Balance impairments often lead to falls related to retropulsion or stumbling, a relative inability to make sufficiently large compensatory balance-correction steps and alter body position effectively [2–4]. These motor symptoms are related to a loss of independence and a decreased quality of life [2, 5, 6].

Clinical guidelines addressing gait-and-balance impairments stress that, alongside pharmacological treatment, physiotherapy and exercise should be given a central role in disease management [7–11]. Exercise can be described as a planned, structured, repetitive, and purposeful physical activity to maintain one or more components of physical fitness, such as strength or balance [10, 12]. Different forms of exercise, ranging from isolated training of specific motor skills to multifaceted exercise like dance or boxing, have repeatedly been shown to improve both motor and non-motor symptoms [6, 12–17]. Current clinical guidelines agree that exercise interventions for pwPD should target multiple components, including gait and balance, endurance, strength, flexibility, and functional-based training like getting up from a chair [7–11], and be specifically designed for pwPD to address their motor symptoms [17].

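### The rank-based fallback for efficacy outcomes sits behind a mixed ANOVA with no outlier protection, so isolated long times on a timed test can stop the t2–t1 comparison from being run

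*Protocol article*

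**What the plan says.** All points are in the Statistical analysis section of the protocol article unless noted.

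- **First step.** Under Potential efficacy, the outcomes "will be subjected to a 2 × 3 mixed ANOVA with the within-subject factor Time (three levels: t0, t1, and t2", with AR-glasses group as the between-subjects factor. The only assumption dealt with here is sphericity: "If Greenhouse–Geisser’s epsilon exceeds 0.75, the Huynh–Feldt correction will be applied; otherwise, the Greenhouse–Geisser correction will be used".
- **Second step.** Paired t-tests serve for "post hoc comparisons of significant main and/or interaction effects involving the factor Time (or paired-sample Wilcoxon tests if data is not normally distributed" by Shapiro–Wilk.
- **Third step.** A test on difference scores, also with a Wilcoxon alternative, follows only under a further condition: "In case t1 differs significantly from t0 as well".
- **Parallel readout.** The article adds that "these comparisons will also be evaluated with Bayesian hypothesis testing". It names no rank-based form.
- **Sample size section.** The calculation is for a direct, one-tailed comparison of two dependent means on the TUG: gain 1.63 s, SD 2.0 s, d = 0.815, 95% power, 18 required, 24 planned.
- **Background.** Gait impairment "can also become episodic when the disease progresses (i.e. freezing of gait"). Freezing is also measured at all three visits as a secondary parameter.

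**The concern.** The protocol foresees non-normal data, but it places the remedy downstream of a normal-theory test that shares the same weakness. A sphericity correction deals with unequal variances of the differences between visits. It does not deal with skew or outliers. A single disturbed walk enters the ANOVA error term at full size, but enters a signed-rank test only as one rank. The data that call for the Wilcoxon test can therefore be the data that prevent it from being run.

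This matters because t2 against t1 is the comparison the sample size was built on. The Future steps section also intends to use the results to choose outcome measures and sample size for a randomised trial. A sensitive timed outcome could look unresponsive because of the order of the tests. The concern is about a rule the article states, not about a detail it leaves out.

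**Working it through.** **1. The plan's own figure.** d = 1.63 / 2.0 = 0.815. For a one-tailed paired t-test at 5%, exact power from the noncentral t distribution is 0.942 at n = 17, 0.953 at n = 18 and 0.987 at n = 24. The stated 18 is reproduced. Because 2.0 s divides the gain directly, it acts as the SD of the paired change.

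**2. Model.** n = 24 (12 per type of glasses); three visits; visit error SD 2.0/√2, so the SD of change is 2.0 s; t2 lower by 1.63 s. The sequence is the mixed ANOVA with the stated Greenhouse–Geisser/Huynh–Feldt rule, then Shapiro–Wilk on t2–t1, then the t-test or Wilcoxon test, all two-sided at 5%. *Assumption, not in the protocol:* each test independently has a 2%, 5% or 8% chance of a delay drawn uniformly from 5–15 s. Of 24 × 3 = 72 tests, that is on average 1.4, 3.6 or 5.8.

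**3. Delays added on top of the 2.0 s.**

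| Tests delayed | Sequence as written | t2–t1 test without the gate |
|---|---|---|
| 0% | 96% | 97% |
| 2% | 76% | 90% |
| 5% | 55% | 79% |
| 8% | 42% | 68% |

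Across the three contaminated rows, a significant Wilcoxon result is blocked by the ANOVA in about 13–25% of trials.

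**4. What those delays do to the SD.** For a delay X uniform on 5–15 s, E(X) = 10 and E(X²) = (15³ − 5³)/(3 × 10) = 108.3. The variance added per test is 108.3p − (10p)², and the variance of the change is 4 plus twice that.

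- p = 0.02: 4 + 2 × 2.13 = 8.25, SD 2.9 s
- p = 0.05: 4 + 2 × 5.17 = 14.33, SD 3.8 s
- p = 0.08: 4 + 2 × 8.03 = 20.05, SD 4.5 s

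The table in step 3 therefore describes a noisier test than the one the plan was sized on.

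**5. Total SD held at 2.0 s.** Error and delays are shrunk together by 2.0/2.87 = 0.70, 2.0/3.79 = 0.53 and 2.0/4.48 = 0.45. The delays become about 3.5–10 s, 2.6–8 s and 2.2–6.7 s. The sequence as written then has power of about 95%, 96% and 96%, and a significant Wilcoxon result is blocked in about 4%, 2% and 1% of trials.

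**6. Sensitivity to the form of delay.**

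- A constant 20 s delay at all visits in three participants leaves the ANOVA significant in 99% of runs. Only delays that vary between visits do damage.
- One, two or three delays of 10–40 s among the 72 values give blocking in 41%, 64% and 68% of runs. By the formula in step 4, with E(X) = 25 and E(X²) = 700, the SD of change is then about 4.8, 6.5 and 7.8 s, far above the plan's 2.0 s.

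**7. Under no true effect.** The t2–t1 comparison without the gate rejects in about 4.6–5.4% of trials, so for that single comparison removing the gate does not inflate error. In fixed-count runs with one to three delays, the ANOVA's Time test rejects in 0.4–4%. The defect is lost power, not false positives.

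**The case against.** The strongest reply concerns size. The 2.0 s is described as an SD over repeated measurements, and nothing says disturbed tests were excluded from it. If it includes them, step 5 applies and the loss is small. This stands. Even in step 3, part of the fall is added noise rather than test order: at 5% delayed, the ungated test itself drops from 97% to 79%.

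A reader might infer from step 3 that the planned power on the TUG is not delivered. The documents do not support that, because the result needs a frequency and length of delays that the protocol does not give, on top of its SD.

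A reader might also see an efficacy-specific slip, since the Feasibility subsection offers a rank test at once: "If the data is not normally distributed, the Mann–Whitney *U*-test will be used". That holds only for its two-group t-tests. The same paragraph prescribes a 2 × 6 mixed ANOVA for weekly scores, again without a fallback. The pattern is consistent: pairwise tests have rank versions and factorial ANOVAs do not.

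The comparison is not wholly lost when the gate closes. The Bayesian evaluation is not stated to depend on a significant ANOVA, partial eta squared is reported, and efficacy is exploratory. This limits the harm, but no robust version of the Bayesian test is named, so it is not shown to repair the problem. Finally, only the TUG was simulated; the result should not be read across to bounded scales or success rates.

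The argument that a condensed article may leave such matters to a fuller document does not dispose of the point. The article itself states the gating rule.

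**Conclusion.** The structural point holds: the only rank-based tests for efficacy are conditional on a significant effect in an ANOVA that has no protection against outliers. For an open-ended timed outcome with isolated long times at single visits, this can suppress the t2–t1 comparison.

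The size is uncertain. At the plan's gain and with 24 participants, a significant Wilcoxon result is blocked in about 1–4% of trials if the 2.0 s already covers disturbed tests. It is blocked in about 13–25% if delays of 5–15 s in 2–8% of tests are additional. The larger rates in step 6 need an SD of change of roughly 5–8 s and are not adopted. With clean normal data, or delays constant across visits, essentially nothing is lost. The sample size calculation is correct for the test it names. This is a modest weakness, worth correcting because correction is nearly free.

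**What to change.** In the Potential efficacy subsection, keep the 2 × 3 mixed ANOVA for Group and Time × Group, which the secondary objective on AR glasses needs. Add that t2–t1 is a planned paired comparison, reported for every efficacy outcome with an estimate and 95% CI whatever the ANOVA shows. Use the paired t-test, or the Wilcoxon test with the Hodges–Lehmann estimate if Shapiro–Wilk rejects normality of the change.

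If a Friedman test is wanted for non-normal outcomes, it should supplement the ANOVA's Time test and not replace the ANOVA, because it has no Group or Time × Group term.

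The cost is about one sentence, with no loss of power when data are normal. This one contrast per outcome is no longer protected by the omnibus test, so the results should be labelled exploratory. In return, the protocol obtains for every outcome the effect-size indications that its Future steps section says the trial should provide.
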